### Background

Due to public stereotypes against people with mental illness (“People with mental illness are stupid”) many people with lived experience of mental disorders internalize these stereotypes, resulting in self-stigma (“Because I am mentally ill, I must be stupid”), shame, secrecy about the illness, and demoralization [1,2]. Self-stigma has serious consequences including giving up life goals, reduced help-seeking, social isolation, poorer clinical outcomes, increased risk for severe mental illness, and suicidality [3]. Stigma mainly is not diagnosis-specific but results from internalizing stereotypes about “the mentally ill.” It is prevalent across severe mental disorders (e.g., schizophrenia, bipolar disorder [4,5]) as well as common mental disorders such as depression or anxiety disorders [6,7]. A transdiagnostic approach to reducing self-stigma is therefore appropriate.

Despite public attention around celebrities disclosing their mental illness, there is no evidence that self-stigma has declined. Our group’s previous work shows that self-stigma and the burden of deciding whether to disclose one’s illness as well as central barriers to coping with public and self-stigma remain [8]. Widely implemented interventions to reduce self-stigma suitable for daily practice are lacking.

The peer-led group program HOP (German: IWS) addresses this gap. HOP supports individuals in deciding whether or not to disclose their mental illness and thus supports participants in their coping with stigma. Our meta-analysis based on five small HOP randomized trials demonstrated that HOP reduces self-stigma on the short term ([9], confirmed in [10]). However, its effectiveness and implementability under real-world conditions have not yet been evaluated in a large pragmatic RCT.

Recent meta-analyses confirm both the severe negative impact of self-stigma on people with mental illness, the healthcare system and society [2], as well as the lack of effective and implemented interventions [11]. Cognitive and psychoeducational self-stigma interventions lack convincing evidence of effectiveness [11]. HOP is innovative in that it supports participants specifically with disclosure decisions—central to coping with both public and self-stigma.

### Specific research questions and hypotheses

Question 1: Does HOP effectively reduce self-stigma among adults with mental illness in a pragmatic real-world trial?

Hypothesis 1: Self-stigma at T1 (after program completion/6 weeks after baseline) will be significantly lower among HOP participants compared to control participants.

Question 2: Does HOP improve secondary clinical and social outcomes?

Hypothesis 2: Compared to control participants, HOP participants will have improved outcomes in depressive symptoms, stigma stress, social inclusion, quality of life, help-seeking intentions, attitudes towards disclosure, and employment.

Question 3: Is HOP effective more than one month after program completion?

Hypothesis 3: At T2 (six months after baseline), self-stigma and secondary outcomes will be significantly improved among HOP participants compared to controls.

Question 4: Is HOP cost-effective in terms of quality of life gains?

Hypothesis 4: HOP is cost-effective in terms of quality of life gains.

Question 5: What facilitates or impedes the implementation of HOP in different settings?

Hypothesis 5: Implementation strategies co-developed with stakeholders during the first six months will result in good reach, study participation, intervention fidelity, and sustainability across settings (inpatient, outpatient, primary care, peer-support settings).

## **Design and Methods**

### **Type I Effectiveness–Implementation Hybrid Trial**

This study uses a hybrid design in which the primary focus is the real-world effectiveness of HOP, and the secondary focus is acceptability, feasibility, and preliminary effectiveness of the implementation intervention.

This hybrid approach allows both main study questions to be addressed simultaneously [12]:

- (1) Does HOP work under pragmatic real-world conditions across regions and settings?
- (2) Which factors support or hinder implementation, and how can implementation be strengthened to ensure successful dissemination and sustainability?

### **Participants / Inclusion and Exclusion Criteria**

Inclusion criteria (all must be met):

- Self-reported mental illness per ICD-10, as self-stigma is a transdiagnostic problem and diagnosis did not predict HOP outcomes in prior studies [9]
- Age 18–60 years (to assess potential employment outcomes)
- written informed consent

Exclusion criteria (none must apply):

- acute suicidality or acute psychotic symptoms
- current substance use that interferes with HOP participation
- Primary substance use disorder without other psychiatric comorbidity
- Intellectual disability (IQ < 70)
- Insufficient German language skills to participate in the group program

### Recruitment

To maximize generalizability, participants will be recruited from:

- (i) inpatient units, day clinics, and outpatient clinics of psychiatric or psychotherapeutic hospitals;
- (ii) private psychiatric and psychotherapeutic practices;
- (iii) general practitioner (GP) practices;
- (iv) peer-support groups and counseling centers for people with mental illness
- (v) print and digital media.

Staff in these settings (including GP practice assistants) will be informed how to inform potential participants and to distribute flyers/posters. Interested individuals will contact study staff, who will conduct consent procedures, data collection, and randomization. Participants receive compensation for assessments and travel reimbursement.

### Study Sites

The study will run at nine sites: four sites in Baden-Württemberg (Stuttgart, Konstanz, Heidelberg, Ulm), four in Bavaria (Günzburg, Augsburg, Munich, Regensburg), and in Leipzig (Saxony).

At each location, the study is conducted in cooperation between EX-IN (a German peer support organization), professionals in the psychiatric-psychotherapeutic care system (psychiatric clinics; registered psychiatrists and psychotherapists), and family doctors (GPs).

### Intervention (HOP + TAU) and Control (TAU only)

HOP is a compact program of 4 sessions (2 hours each) [9]. Sessions 1–3 take place in weeks 1, 2, and 3, and session 4 (booster) in week 6. Groups consist of approximately 4–8 participants and are led by two peers—trained adults with lived experience of mental illness. Peer group facilitators are recruited via mutual support networks (e.g., “EX-IN”). They receive two days of structured training and continuous supervision throughout the study.

### Main content of HOP sessions:

- Lesson 1: weighing pros/cons of disclosure in different situations
- Lesson 2: levels of disclosure and identifying appropriate recipients
- Lesson 3: telling one’s story
- Lesson 4: booster session to reflect and update disclosure decisions

HOP does *not* aim to encourage disclosure; rather, participants learn to make strategic, context-dependent decisions for or against disclosure in different settings.

Control condition: TAU only. Participants may continue any ongoing psychiatric-psychotherapeutic or GP treatment or peer support.

### Recruitment of HOP group facilitators

The study collaborates closely with regional German EX-IN associations (Bavaria, Baden-Württemberg, Saxony). EX-IN members, trained as peer-support workers, are well suited to facilitate HOP groups and to support implementation through their community networks.

### Randomization

Immediately after baseline assessment (T0), participants will be block-randomized 2:1 (HOP:control). This facilitates the beginning of new HOP groups and supports recruitment by offering a higher probability of receiving HOP. Randomization is performed by closed opaque envelopes, provided by the Institute of Biometry, University of Ulm. A block randomization with varying block sizes (3, 6 or 9) will be used.

### Assessment Times

T0: Baseline before randomization

T1: 6 weeks after baseline, and after the HOP booster session for HOP participants

T2: 6 months after baseline

### Effectiveness Outcomes

The primary endpoint is self-stigma at T1, assessed via the 5-item self-concurrence subscale of the Self-Stigma of Mental Illness Scale–Short Form [15].

Secondary outcomes include:

- Quality of life (EUROHIS-QOL) [16]
- Depressive symptoms (PHQ-9) [17]
- Stigma stress (Stigma Stress Scale, 8 items) [18]
- Shame [19]
- Attitudes toward professional help-seeking (General Help-Seeking Questionnaire, 3-item subscale) [20,21]
- Attitudes toward disclosure [22]
- Recovery (Self-Identified Stage of Recovery, Part B, 4 items) [23]
- Social inclusion (Experiences of Social Inclusion Scale, 10 items) [24]
- Employment status [25]

Among participants in the HOP condition, program satisfaction is assessed at T1.

For details on the instruments used, see [9].

### Sample Size

A previous German-speaking adult HOP RCT yielded an effect size of  $d = 0.4$  for self-stigma 6 weeks after baseline [13]. With power = 0.80, alpha = 0.05 (two-sided), and a 12% sample-size increase for 2:1 randomization, the required total sample is 224 participants (149 HOP, 75 control) [13].

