### Statistical Analysis

The primary endpoint (self-stigma at T1) will be analyzed via intention-to-treat using mixed models for repeated measures (MMRM), with each HOP group as a nesting variable and adjustment for site. The two-sided significance threshold is  $p < .05$ .

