### Implementation Outcomes

Outcomes will be assessed quantitatively and qualitatively [30,31]. Initial interviews inform a questionnaire assessing barriers and facilitators, completed by participants and stakeholders. Fidelity will be measured with established checklists [13,26,32]. Adherence and dropout will be documented. The proportion of contacted institutions (e.g., GP practices) entering cooperation will be recorded.

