### Gender Aspects

Reviews do not show consistent gender effects on self-stigma [2]. However, HOP effects on depression appeared gender-specific in a California study (improvements for women only) [32]. Self-stigma may also impede help-seeking more strongly in men [2]. Gender (female, male, diverse/other) will therefore be analyzed regarding effectiveness, implementation, and dropout. We will aim for gender balance among advisory board members, study staff, and HOP group facilitators.

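### The 80% power stated for 224 participants is calculated for independent participants with complete T1 data; it allows nothing for the HOP-group nesting in the primary model or for missing T1 values

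*Protocol*

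**What the plan says.** The Sample Size section takes d = 0.4 for self-stigma six weeks after baseline from an earlier German-speaking trial of the programme. It then sets the error rates, "With power = 0.80, alpha = 0.05 (two-sided"), and reaches the total through "a 12% sample-size increase for 2:1 randomization, the required total sample is 224 participants (149 HOP, 75 control"). No other inflation is mentioned.

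Three other sections bear on that figure:

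- Intervention and Control: HOP is given in groups. "Groups consist of approximately 4–8 participants". The control arm receives usual treatment only and has no study groups.
- Statistical Analysis: the primary endpoint is analysed by intention to treat with an MMRM "with each HOP group as a nesting variable and adjustment for site".
- Implementation Outcomes: "Adherence and dropout will be documented". Gender Aspects adds that gender "will therefore be analyzed regarding effectiveness, implementation, and dropout". Neither section gives a rate.

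**The concern.** The power calculation and the primary analysis describe different data. The calculation treats all 224 participants as independent and observed at T1. The analysis model allows HOP participants who share a group, and its two peer leaders, to be correlated. It will also have to deal with any T1 value that is missing. Both features reduce the information on the treatment difference, and the 12% increase is assigned to the allocation ratio alone.

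The Background presents this as the large real-world trial that is still lacking after five small ones, and the section on use of results links roll-out across Germany to its outcome. Readers will use the stated 80% to judge how informative a non-significant result is, so it should be the power of the analysis that will be run.

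**Working it through.** **Inputs from the protocol.** d = 0.4, power 0.80, two-sided alpha 0.05, 12% increase, 149 HOP and 75 control (Sample Size); 2:1 allocation (Randomization); groups of about 4–8 in the HOP arm only (Intervention and Control); HOP group as nesting variable (Statistical Analysis).

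**Inputs the protocol does not give, assumed here.** Within-group ICC 0.02 to 0.10; T1 loss 0 to 20%, equal in both arms; mean group size m = 6 (middle of 4–8), with 8 as a check.

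**Step 1: reproduce 224.** A 1:1 two-sample t-test with d = 0.4 needs 99.08, so 100 per arm and 200 in total. 200 × 1.12 = 224. The theoretical factor for 2:1 allocation is (1 + 2)² / (4 × 2) = 1.125, so the 12% is the allocation penalty and nothing more.

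**Step 2: power at 149:75, independent and complete.** SE = √(1/149 + 1/75) = 0.1416; 0.4 / 0.1416 = 2.82; t-test power on 222 df = 0.803. The margin is thin: with two of the 224 values missing, power is 0.7996.

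**Step 3: add nesting and loss.** Let L be the loss proportion, so that n_H = 149(1 − L), n_C = 75(1 − L) and the observed group size is m(1 − L). Only the HOP arm carries a design effect:

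DE = 1 + [m(1 − L) − 1] × ICC

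SE = √(DE / n_H + 1 / n_C)

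Where ICC > 0, power uses Satterthwaite degrees of freedom with n_H / [m(1 − L)] groups in the HOP arm.

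Example with m = 6, ICC 0.05, L = 0: DE = 1 + 5 × 0.05 = 1.25; SE = √(1.25/149 + 1/75) = 0.1474; 0.4 / 0.1474 = 2.71; power 0.766.

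Results without baseline adjustment:

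| m | ICC | T1 loss | Power at d = 0.4 | Effect detectable with 80% power |
|---|---|---|---|---|
| – | 0 | 0 | 0.803 | 0.398 |
| 6 | 0.02 | 0 | 0.785 | 0.408 |
| 6 | 0.05 | 0 | 0.766 | 0.417 |
| – | 0 | 10% | 0.760 | 0.420 |
| 6 | 0.02 | 10% | 0.743 | 0.429 |
| 6 | 0.05 | 10% | 0.725 | 0.438 |
| – | 0 | 20% | 0.710 | 0.446 |
| 6 | 0.05 | 20% | 0.678 | 0.463 |
| 6 | 0.10 | 20% | 0.652 | 0.477 |
| 8 | 0.10 | 20% | 0.629 | 0.490 |

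A normal approximation that holds group size fixed gives similar values, for example 0.731 for ICC 0.05 with 10% loss.

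**Step 4: what the baseline measurement could recover.** Suppose that d = 0.4 is on the unadjusted SD and that using T0 multiplies the variance by 1 − r², where r is the T0–T1 correlation. With m = 6, the r that brings power back to 0.80 is:

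- 0.29 for ICC 0.05 with no loss
- 0.36 for ICC 0.02 with 10% loss
- 0.41 for ICC 0.05 with 10% loss
- 0.50 for ICC 0.05 with 20% loss
- 0.54 for ICC 0.10 with 20% loss

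At r = 0.3, ICC 0.05 with 20% loss still gives only 0.72. Applying 1 − r² to the between-group variance as well is favourable to the plan; if baseline explains less of that part, the recovery is smaller.

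**The case against.** The strongest reply is that the planned analysis is a repeated-measures model with self-stigma measured at T0 and T1. The calculation omits the gain from T0 just as it omits the loss from nesting, and the two work in opposite directions. A moderate T0–T1 correlation would bring power back to 80% or above. This stands, and it limits the conclusion: a reader might infer that the trial is underpowered or will not deliver 80%, and the documents do not show that. Equally, they do not show the reverse. No section states a T0–T1 correlation, says how T0 enters the model, or relies on such a gain.

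A second reply concerns loss. A reader might infer that the protocol expects dropout at T1. It says only that dropout will be documented and analysed. The first statement sits among the implementation outcomes, where it can mean leaving the programme; under intention to treat, someone who leaves HOP can still give T1 data. T1 is only six weeks after baseline, and every participant is paid €20 per assessment. So the 10% and 20% used above are assumptions, and they account for most of the larger shortfalls. What remains is that the calculation tolerates practically no loss, and that the section does not say whether 224 counts people randomised or people with T1 data.

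A third reply is that MMRM handles missing data. Under missing at random it limits bias, but it does not return all the lost T1 information.

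Finally, details of this kind can be left to a statistical analysis plan. Here, however, the protocol gives a finished calculation with its inputs and result, and that calculation does not match the primary model in the section that follows it.

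**Conclusion.** The point holds as a mismatch between the power statement and the planned analysis. It is not an arithmetic error: 200 × 1.12 = 224 is correct. The calculation omits a design feature that the protocol itself builds into the model, and it assumes complete T1 data without saying so.

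The part that rests on the design alone is small: at groups of 6, clustering costs about 2 points of power at ICC 0.02 and about 4 at ICC 0.05. To say that power is well below 80% requires an assumed T1 loss, or a larger ICC, together with no gain from baseline. Over the assumptions shown, with groups of 6, power without baseline adjustment runs from 0.785 down to 0.652, and the detectable effect from about 0.41 to 0.48 (0.49 with groups of 8). A T0–T1 correlation of about 0.3 to 0.5 would restore 80% in all but the harshest cases. The true net power cannot be determined from the protocol.

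This should be fixed, but it does not threaten the validity of the design, endpoint or analysis.

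**What to change.** Keep 224 and rewrite the power statement in the Sample Size section so that it refers to the model in the Statistical Analysis section. State the assumed within-group ICC (HOP arm only), the mean group size, the assumed T1 loss and, if the gain from T0 is to be counted, the assumed T0–T1 correlation and how T0 enters the model. Give the resulting power, preferably over a short range, because the protocol cites no source for these values. Say whether 224 is the number randomised or the number with T1 data.

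The cost is one reworded paragraph, and the stated power may become slightly less favourable. If 224 turns out to mean participants with T1 data, the number to randomise must be given as well and will be larger; otherwise no extra participants are needed.

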### Statistical Analysis

The primary endpoint (self-stigma at T1) will be analyzed via intention-to-treat using mixed models for repeated measures (MMRM), with each HOP group as a nesting variable and adjustment for site. The two-sided significance threshold is  $p < .05$ .

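### The primary MMRM names HOP group and site but not baseline self-stigma; stating how T0 enters would be a free gain in precision

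*Protocol*

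**What the plan says.** The Statistical Analysis section of the protocol gives the primary analysis in two sentences. The method: "The primary endpoint (self-stigma at T1) will be analyzed via intention-to-treat using mixed models for repeated measures (MMRM". The terms named: "with each HOP group as a nesting variable and adjustment for site". The second sentence sets the two-sided significance level.

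Effectiveness Outcomes defines the endpoint: "The primary endpoint is self-stigma at T1, assessed via the 5-item self-concurrence subscale". Assessment Times lists three measurements, the first being "T0: Baseline before randomization", followed by T1 at six weeks and T2 at six months. Neither the Statistical Analysis section nor any other part of the protocol says whether T0 self-stigma is a covariate, one of the repeated responses, or absent from the model.

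Sample Size rests on d = 0.4 and is stated as follows: "With power = 0.80, alpha = 0.05 (two-sided), and a 12% sample-size increase for 2:1 randomization", "the required total sample is 224 participants (149 HOP, 75 control". It uses no baseline correlation.

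**The concern.** The same five-item scale taken six weeks earlier is likely to be the strongest single predictor of T1 self-stigma, and the trial collects it from everyone before allocation. The protocol does name an adjustment variable, site, but not this one.

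The method name does not settle the matter, because models with different precision all fit the wording:

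- T1 and T2 as responses with no baseline term. The T1 contrast is unadjusted.
- T0, T1 and T2 as responses with separate arm means at every time. The T1 contrast is again no more precise than an unadjusted one. If the arm-by-time change from T0 is tested instead, the variance can be larger or smaller than unadjusted, depending on rho.
- T0 as a covariate, or as a response with a common mean in both arms. Only these condition on baseline and gain precision.

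The choice therefore affects the width of the primary confidence interval and the power. It also decides whether a chance T0 difference between the arms carries into the estimate in the trial at hand.

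**Working it through.** **Inputs from the protocol.** d = 0.4, two-sided alpha 0.05, power 0.80, 12% inflation, and 149 HOP and 75 control (Sample Size). Allocation: "participants will be block-randomized 2:1 (HOP:control" (Randomization). Groups of about 4–8 (Intervention and Control section).

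**Assumed, not in the documents.** T0–T1 correlation rho of 0.3 to 0.7. For the second power calculation only: intraclass correlation (ICC) 0.05 within HOP groups, groups of 6, and 85% retention.

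**Step 1: the plan's own figure.** A two-sample t-test at 1:1 needs 99.08, so 100, per arm. The total is 200, and 200 × 1.12 = 224, which reproduces the stated size. Power at 149/75 with no baseline adjustment: variance = 1/149 + 1/75 = 0.02004, SE = 0.1416, and 0.4/0.1416 = 2.825. Power is 80.7% by the normal approximation and 80.3% by the t distribution.

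**Step 2: variance of the T1 effect relative to unadjusted (SD equal at T0 and T1).**

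- T1 alone, or T0 as a response with separate arm means and the T1 contrast tested: 1.00. A generalised least squares check gives 1.00 for the latter at rho 0.5 and 0.7.
- Change from T0: 2(1 − rho). This exceeds 1 when rho is below 0.5.
- T0 as a covariate, or as a response with equal arm means at T0: 1 − rho². The least squares check for the constrained model gives 0.75 at rho 0.5 and 0.51 at rho 0.7, the same as covariate adjustment.

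The change contrast is always less precise than baseline adjustment when rho is below 1, because 2(1 − rho) − (1 − rho²) = (1 − rho)² > 0.

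**Step 3: power at d = 0.4.** The plain column multiplies 0.02004 by 1 − rho². The last column uses the partially nested variance (1 − rho²) × [(1 + 5 × 0.05)/(0.85 × 149) + 1/(0.85 × 75)] = (1 − rho²) × (1.25/126.65 + 1/63.75) = (1 − rho²) × 0.02556.

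| rho | change | adjusted | variance removed | power, 149/75 | power with ICC 0.05, groups of 6, 85% retained |
|---|---|---|---|---|---|
| no adjustment | – | 1.00 | 0% | about 80% | about 70–71% |
| 0.3 | 1.40 | 0.91 | 9% | 84% | 74–75% |
| 0.5 | 1.00 | 0.75 | 25% | 90% | 82% |
| 0.6 | 0.80 | 0.64 | 36% | 94% | 88% |
| 0.7 | 0.60 | 0.51 | 49% | 98% | 94% |

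Worked line for rho 0.5, last column: 0.75 × 0.02556 = 0.01917, SE = 0.1384, and 0.4/0.1384 = 2.889. Power is about 82%.

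The last column assumes that adjustment shrinks the between-group and within-group components alike. If the between-group component is not reduced at all, the adjusted figures are 1 to 2 points lower, for example about 81% at rho 0.5.

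**The case against.** The strongest objection is that this is silence, not a stated error. The section is a two-sentence summary. It also leaves out arm, visit and arm by visit, which any such model must contain, so the terms it names need not be the full list. How T0 enters may be set out in a statistical analysis plan that is not shown. This stands to the extent that a reader might infer that the model adjusts for site alone and excludes baseline, and the protocol does not say that. A repeated-measures model with T0 as a response and a common baseline mean fits the wording and loses nothing.

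Three other strong readings also fail:

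- A reader might conclude that at least a quarter of the variance is being given away. That needs rho of 0.5 or more, and no correlation is reported. At 0.3 the figure is 9%.
- A reader might conclude that the sample size is wrong. It is not: 224 was derived without any baseline correlation, and it reproduces.
- A reader might conclude that the primary contrast is undefined. Hypothesis 1, Effectiveness Outcomes and Statistical Analysis all point to the difference between arms at T1. What is open is how that difference is adjusted.

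Chance imbalance at T0 does not bias a randomized comparison on average, nor does it spoil the type I error. The gain is in precision.

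What the objection does not remove is that the protocol chose to name an adjustment and did not name the variable likely to matter most. Of the models that fit its wording, only some use T0 efficiently.

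**Conclusion.** The point holds as a free improvement, not as an error. As written, the primary model either leaves out T0 self-stigma or includes it in a way the protocol does not specify. Conditioning on T0 would remove rho² of the variance: 9% to 49% for rho between 0.3 and 0.7. At the planned 149/75 that is a rise in power from about 80% to between 84% and 98%.

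Under the assumed clustering and retention, power without adjustment is about 70–71%. Adjustment brings it back above 80% if rho is about 0.5 or more, but only to 74–75% if rho is 0.3. All these figures rest on the assumed rho; the clustered ones rest also on the assumed ICC, group size and retention. If the unseen analysis plan already conditions on T0, nothing is lost and only the protocol's wording needs to catch up.

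**What to change.** Add to the Statistical Analysis section a sentence such as: The model includes T0 self-stigma (as a baseline-by-visit covariate, or as a response with arm means constrained equal at T0), site, visit and arm by visit, with HOP group as the nesting factor; the primary estimate is the adjusted difference between arms at T1.

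Choose one of the two forms for T0 and fix it before outcome data are seen. Treat the continuous secondary outcomes in the same way, each with its own T0 value.

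The cost is one sentence. T0 is already collected, and neither the sample size nor the conduct of the trial changes.
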